### Quality Control

Several procedures are employed to ensure the quality of the study data, thus maximizing the validity and reliability of the program delivery and outcome assessments. These are:

• Formation of the professionals participating in the study.

• Use of an electronic data collection system with a system of warnings and internal coherency norms.

• Regular meetings and mailings between members of the study group and all participating centres.

### Ethical Aspects

In the first contact with the pregnant woman, she will be given information about the study and will sign an informed consent form if she wishes to participate. The informed consent will describe the ethical conditions and the participant's right to intimacy, anonymity, confidentiality, withdrawal and information. The investigators are committed to respecting the norms of good clinical practice, as well as the requirements of the Helsinki Declaration. The protocol has been evaluated and approved by the Ethical Committee of Scientific Research of the Primary Care Research Institute Jordi Gol (Barcelona, Spain). Confidentiality of data: Only the investigators and monitors/auditors of the study will have access to the data of the subjects who agreed to participate.

## Discussion

One of the strengths of the present study is its design which is pragmatically oriented with respect to the needs of time and material resources.

Another strength of the study is the large number of midwives and patients involved, reinforcing the external validity of the data.

Since no register of women in the first trimester of pregnancy is available, selection of the study population can not be approached with a simple randomised sample but will rather be performed by consecutive sampling which could lead to a selection bias, the self-selection of the volunteer. To determine the possible presence of such a bias the administrative, sociodemographic and obstetric variables of the women who refuse to participate in the study will be analysed.

To increase the validity and reliability of the data collection of the hygienic-dietetic habits by individualised interview, the midwives have been especially trained in this task following a training session prior to initiation of the pilot study and a support investigator will be available to solve any doubts which may arise.

The difficulty in determining iodine intake through diet will be compensated by the determination of iodine levels in urine which is considered a good marker of iodine ingestion according to the WHO, UNICEF and ICCIDD [4,45].

To avoid the phenomenon of contamination which may appear when the intervention influences the subjects in the control group (frequent when the same work centre of the professionals belongs to different study groups), randomisation of the intervention will be performed by the PCN and not by study subjects. Although the unit of randomisation is the primary care unit, the intervention is given at the individual level and the outcomes are also measured at this level. The estimation of the design effect will be taken into account in all the main analyses.

Since participant losses and withdrawals randomly occur, any subject exclusion from the analysis may later affect group comparability. To preserve this all the patients included in the study will be evaluated according to the intention to treat principle and thus, all the patients will be analysed as pertaining to the group to which they were initially assigned independently of the treatment they have actually received.

Lastly, it should be pointed out that if the questionnaire on the nutritional status of iodine is found to be valid and reliable, it may be a valuable tool for the detection of iodine deficiency during gestation in midwife consulting offices without the need to request ioduria. The midwife may thereby intervene rapidly and adequately in such a situation informing the woman as to the role of iodine in foetal development and underline the importance of foods rich in iodine.

If the results obtained demonstrate the presence of iodine deficiency in an important proportion of the gestating population, this would support the implementation of preventive interventions to improve and intensify health care education programmes in pregnant women as well as to make the public health authorities aware of the importance and repercussions of iodine deficiency and attempt to systematically implement supplementation of foods containing iodine, a measure which already prevails in some countries such as Argentina.

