Until several years ago the fundamental problem of iodine deficiency lay in endemic goitre but in the last decades studies have demonstrated a wide spectrum of disorders caused by iodine deficiency during pregnancy such as an increase in the number of abortions and dead foetuses, an increase in neonatal morbimortality and hearing defects in infants [20], a reduction in intellectual capacity and growth, congenital abnormalities with permanent neuromotor damage [21,22] as well as the attention deficit syndrome and hyperactivity [23,24]. According to the WHO, lack of iodine is the most frequent cause of mental retardation and irreversible brain lesions in the world [4].

Recent studies have demonstrated that iodine intake during gestation is low, even in areas where theoretically there are institutional prevention programmes to promote the consumption of iodised salt [18,25-27]. All these studies have been determining factors for the Spanish and the Catalan Societies of Endocrinology and Nutrition, the Spanish Society of Gynaecology and Obstetrics and the Ministry of Health and Social Policies to consider pregnant women as a risk group for disorders as a consequence of iodine deficit and to thereby recommend a diet rich in iodine and iodised supplements. Iodine deficiency in this population, albeit moderate, represents a high risk of cerebral lesions in the foetus [19,22].

The contribution of the quantity of iodine necessary for a good health status has been included as a basic human right: "All children have the right to an adequate intake of iodine to ensure normal development", especially children yet to be born and thus, "All mothers have the right to adequate iodine ingestion during gestation to ensure that their child achieves an optimum mental development" [28,29].

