### Sample size calculation

The sample size has been calcuated by multipying the size of a randomized simple design by the design effect. For the simple randomized design an alpha error of 0.05 and a beta error of 0.20 in a bilateral contrast are considered, requiring 204 pregnant women in the intervention group and 204 in the non intervention group to detect a difference greater than or equal to 15% in the prevalence of iodine deficiency between the two. After extensive review of the literature on group educational interventions in a pregnant population, the investigative team [37-40] considered that the intervention to be undertaken in the intervention group will achieve an improvement of at least 15% in hygienic-dietetic habits and thus in the levels of ioduria. A proportion of iodine deficiency of 44% in the non intervention group is assumed as indicated by studies performed in populations in the Pyrenees and the coast of the Maresme, areas near the study setting [18]. A loss to follow up of 15% has been estimated. Using an intracluster correlation coefficient of 0.05 [41-43], and based on an average of 25 pregnant women per PCT, the design effect is 2.2. Therefore, 898 pregnant women and 36 PCT are needed.

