- Request for ioduria during the first trimester: the midwife will request an ioduria test and will explain the woman how to correctly collect the urine and will program the appointment for the second trimester visit of the pregnancy. On receipt of the ioduria results the midwife will note these in the EDCF. In cases in which iodine deficiency is detected the midwife will duly intervene, thus the reason for including the telephone number of the pregnant woman in the questionnaire. If iodine supplementation is indicated the administration will begin on collection of the first urine sample to avoid underestimation of the prevalence of iodine deficiency in the first trimester. Ioduria will be analysed using the Benotti&Benotti method performed in the laboratory of the Hospital Clinic of Barcelona.

* **PHASE 5. Group Education Intervention (only in IG)**: the coordinating midwives in each zone will be responsible for performing the educational workshops on hygienic-dietetic habits in the pregnant women in the intervention group. This workshop will be held in the first trimester since this is when organogenesis is produced and is therefore the time of greatest risk for the appearance of alterations in the development of the foetal central nervous system in cases of maternal iodine deficiency. The content of the educational workshop will be the same to avoid a variation in information and transmission of knowledge to the pregnant women, that is, to ensure receipt of homogeneous information by the pregnant women.

* **PHASE 6. Follow up (in IG and NIG)**: if a pregnant woman does not attend the appointment she will be called by telephone and if she cannot be contacted after 10 attempts she will be withdrawn from the study. The interview on hygienic-dietetic habits will be given in the second and third trimester appointments and determination fo ioduria will be requested. The reasons for participant withdrawal will be reported and a flow chart of the patients will be created throughout the study.

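### The Discussion says losses occur at random, against its own reasoning and the Background, and the Phase 6 withdrawal rule can turn one missed visit into a lost third-trimester ioduria

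*Protocol article*

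**What the plan says.** Four statements in the protocol article bear on this point.

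- **Discussion, on losses:** "Since participant losses and withdrawals randomly occur, any subject exclusion from the analysis may later affect group comparability". The text then turns to intention to treat as the way to preserve comparability: every included woman will be evaluated in the group to which she was first allocated, whatever treatment she received.
- **Description of the Study, Phase 6:** a woman who does not attend an appointment is telephoned, and "if she cannot be contacted after 10 attempts she will be withdrawn from the study". The same paragraph requires reasons for withdrawal to be reported and a participant flow chart.
- **Background:** among the disorders attributed to iodine deficiency in pregnancy is "an increase in the number of abortions and dead foetuses".
- **Sample size calculation:** "A loss to follow up of 15% has been estimated".

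Women enter in the first trimester. Habits and ioduria are assessed again in the second and third trimesters. The dependent variable is iodine deficiency, defined as ioduria below 150 μg/L.

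**The concern.** If losses really occurred at random, excluding the lost women would reduce precision but would not make the groups systematically different. The sentence draws the opposite consequence from its own premise. Either the premise is wrong or the wording is.

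The premise is also hard to square with the Background. Pregnancy loss falls within follow-up, and the article ties it to the condition that the trial measures.

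The Phase 6 rule then adds missing outcomes that need not be missing. As written, a woman who misses the second-trimester visit and cannot be reached by telephone is out of the study, with no provision for a third-trimester interview and urine sample if she comes back to antenatal care. That conflicts with the promise to evaluate every included woman. Analysing a woman in her assigned group settles which arm she counts in, but it does not supply an ioduria that was never measured.

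At stake are the deficiency prevalence in the later trimesters and, if the loss mechanism differs between arms, the estimated effect of the workshop.

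**Working it through.** **1. The plan's own figure.** Inputs from Sample size calculation: "an alpha error of 0.05 and a beta error of 0.20 in a bilateral contrast are considered"; "A proportion of iodine deficiency of 44% in the non intervention group is assumed"; the aim is "to detect a difference greater than or equal to 15% in the prevalence of iodine deficiency between the two", taken here as 44% against 29%.

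- Uncorrected n per arm = [1.96·√(2·0.365·0.635) + 0.8416·√(0.44·0.56 + 0.29·0.71)]² / 0.15² = (1.334 + 0.566)² / 0.0225 ≈ 160.5, so 161.
- With continuity correction: (n/4)·[1 + √(1 + 4/(0.15·n))]² ≈ 173.6, so 174.
- Loss allowance: 173.6/0.85 = 204.2, or 205 if 174 is used. The plan states "requiring 204 pregnant women in the intervention group and 204 in the non intervention group".
- Design effect: 1 + (25 − 1)·0.05 = 2.2. Total: 408·2.2 = 897.6, so 898. Clusters: 898/25 = 35.9, so 36.

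The figure reproduces. (44% against 59% without the correction also gives 174.) The 204 therefore already includes the 15% allowance. Working back, 449 per arm × 0.85 = 381.65, and 381.65/2.2 = 173.5, against the 174 needed. Power is planned on women with an observed outcome, and about 67 per arm are expected to have none. The sample size itself is not affected by this point.

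**2. What loss related to the outcome would do.** The documents give no rate of deficiency among lost women, so the relative risks below are assumptions. Let p be the true deficiency rate in an arm, L = 0.15 the overall loss in that arm, and r the risk of loss for deficient women relative to the others.

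- Loss among non-deficient women: q = L/(1 − p + r·p). Loss among deficient women: r·q.
- Observed prevalence: p·(1 − r·q)/(1 − L).

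Example with r = 2. Control arm: q = 0.15/1.44 = 0.1042, r·q = 0.2083, observed 0.44·0.7917/0.85 = 41.0%. Intervention arm: q = 0.15/1.29 = 0.1163, r·q = 0.2326, observed 0.29·0.7674/0.85 = 26.2%.

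| Assumed r (control / intervention) | Observed control | Observed intervention | Difference, points |
|---|---|---|---|
| 1 / 1 | 44.0% | 29.0% | 15.0 |
| 1.5 / 1.5 | 42.2% | 27.4% | 14.8 |
| 2 / 2 | 41.0% | 26.2% | 14.8 |
| 3 / 3 | 39.4% | 24.4% | 15.0 |
| 1 / 2 | 44.0% | 26.2% | 17.8 |
| 2 / 1 | 41.0% | 29.0% | 12.0 |

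With no true effect (44% in both arms), r of 1.5, 2 or 3 in the intervention arm only gives a spurious difference of 1.8, 3.0 or 4.6 points.

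**3. Reading the table.** The same mechanism in both arms lowers each prevalence by about 2 to 5 points and leaves the difference almost unchanged. The difference moves materially only when the mechanism differs between arms, and the direction depends on which arm it acts in.

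**The case against.** The strongest reply is that the sentence is a slip. Its second half, and the turn to intention to treat, make sense only if losses do *not* occur at random, and the article has other language errors. No analysis in Statistical analysis is said to depend on random loss. This is plausible but cannot be confirmed from the text. If it is right, the printed sentence says the reverse of what was meant and still needs correcting.

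A reader might go further and infer three things that the documents do not support.

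- **That only completers will be analysed.** Nothing says so. Statistical analysis and the Discussion both promise intention to treat. How women without a later ioduria enter that analysis may be set out in a full plan that is not shown, so the absence of an imputation or sensitivity method is not a defect here.
- **That outcome-related loss inflates the workshop effect.** The pregnancy-loss link would act in both arms, and the table shows that this hardly moves the difference. Only the intervention group is invited to a workshop, and the Background names variable attendance as a difficulty of group education, so a difference in loss between arms is conceivable. The article does not say that it will occur, and bias could run either way.
- **That Phase 6 discards data or removes women readily.** The rule applies only after 10 contact attempts, and reasons are recorded. The text does not say that data already collected are dropped, nor what happens if a withdrawn woman returns. It also does not say that pregnancy loss is what makes women unreachable.

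What stands is the contradiction in the Discussion, its poor fit with the Background, and a stated withdrawal rule that works against the promise to evaluate everyone.

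**Conclusion.** The point holds in limited form. The random-loss statement is internally inconsistent and unsupported. The Phase 6 rule, as written, can lose a third-trimester outcome because of one missed second-trimester visit.

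With 15% loss and an assumed relative risk of 1.5 to 3 in both arms, prevalence is understated by about 2 to 5 points and the difference stays near 15. With a relative risk of 2 in one arm only, a true 15 points appears as 17.8 or 12.0.

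Three limits apply:

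- The relative risks are illustrative, not estimates.
- The first-trimester prevalence is measured before this loss and is not touched. The understatement concerns the later trimesters. It bears on general objective 2 in the Abstract's wording, which covers pregnancy as a whole; the Objectives section words it as the first three months.
- The calculation treats every lost woman as having a definable deficiency status. Where the pregnancy has ended, a later gestational ioduria does not exist and should not be counted as missing.

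This is an inexpensive improvement to follow-up and wording. It does not show that the planned analysis is invalid.

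**What to change.** 1. **Discussion:** remove the statement that losses occur at random or, if a word was dropped, correct it.
2. **Phase 6:** a woman who misses a visit and is not reached stays in the study. She is interviewed and sampled at her next attended antenatal visit, unless she withdraws consent or is no longer pregnant.
3. **Statistical analysis:** include all available second- and third-trimester ioduria in the planned multilevel analysis, by assigned group.
4. **Flow chart:** report pregnancy losses by arm, separately from other losses, and do not impute ioduria after a pregnancy has ended.

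The cost is somewhat more tracking of women between visits and a little more analysis and reporting work. No visits are added, and the sample size does not change.

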## Abbreviations

**(CNS)**: Central Nervous System; **(EDCF)**: Electronic Data Collection File; **(ICCIDD)**: International Council for Control of Iodine Deficiency Disorders; **(IG)**: Intervention Group; **(NIG)**: Non Intervention Group; **(PCC)**: Primary Care Centres; **(PCN)**: Primary care nurses; **(PCT)**: Primary Care Team; **(TSH)**: Thyroid-stimulating Hormone; **(UNICEF)**: United Nations International Children's Emergency Fund; **(WHO)**: World Health Organization;
